## Abstract

**Background:**

Community interventions are often promoted as a way of reducing loneliness and social isolation in our neighbourhoods. However, those community interventions are rarely examined within rigorous study designs. One strategy that holds the potential to reduce loneliness and can promote health and wellbeing is doing acts of kindness. The current study involves evaluating the impact of kindness acts on loneliness in community-dwelling individuals using an online social networking platform.

**Methods:**

This study is made up of three randomised controlled trials conducted in three countries. Each randomised controlled trial has two arms (intervention vs waitlist control) and is designed to compare the effectiveness of the KIND challenge, which involves doing at least one act of kindness per week within a four-week period. This study will recruit users of an online community, be randomised online, and will be conducted using online assessments. We will first explore the effects of the intervention on the primary outcome of loneliness, followed by secondary outcomes, social isolation, neighbour relationship quality and contact, mental health symptoms, stress, quality of life, and positive affect. Further, we will assess the feasibility, acceptability, and safety of the KIND Challenge.

**Discussion:**

This study, designed to evaluate the impact of kindness on the community, will be the first large scale randomised control trial conducted across three countries, Australia, UK, and USA. It will examine the potential of community-led interventions to reduce loneliness, improve social isolation, and promote neighbourhood cohesion, health, and wellbeing, which is especially crucial during the COVID-19 public health crisis.

**Trial registration:**

Clinical Trials Registry. NCT04398472. Registered 21st May 2020.

**Supplementary Information:**

The online version contains supplementary material available at 10.1186/s12889-021-11489-y.

## Background

The health effects of social isolation are well known to be detrimental to health outcomes [1, 2] and more recently, the evidence for perceived social isolation, “loneliness”, on poor health outcomes, has also been growing [3, 4]. Those who lack strong social connections show a 50% increased risk of an earlier death, and when we consider loneliness specifically, there is a 26% increase in early death after taking into consideration factors like age, gender, and ethnicity [5]. Prolonged loneliness experienced over the course of childhood and adolescence is associated with poor health behaviours and poorer mental health during early adulthood [6, 7]. There are a range of physical health indicators associated with loneliness. For example, cardiovascular health indicators including systolic blood pressure, heart rate, heart contractibility, and cardiac output are all impaired in lonely people [2, 8–10].

The negative impacts of loneliness on health outcomes are seen across the lifespan [11]. While there may be differences in the prevalence and source of loneliness at different ages [11], our communities are one place where people of all ages can take an opportunity to connect with others [12], building connections with neighbours and attaining a sense of belonging. Being well connected in a community setting can provide an important source of social interaction and can mitigate against social isolation and feelings of loneliness [13]. According to the belongingness hypothesis, individuals need a sense of connection to larger groups or a community as well as close interpersonal relationships to achieve a sense of belonging. In a survey of 2840 people in the UK, the variable most consistently associated with having higher subjective wellbeing was ‘feeling part of a community’ [14]. Community connectedness can be increased and doing so can bring about great social and personal benefits to members of the community [14]. This is commonly achieved by ensuring accessibility and equity for all groups in the community. For example, local councils may improve access to home and community care services for people from diverse backgrounds and with diverse needs and run events such as community festivals that promote community connectedness [15]. Those methods rely on the active participation of community members, and despite best efforts, there are challenges faced in engaging those who are isolated and most in need of these opportunities.

Previously, a sense of community would have been established through face-to-face contact, but the use of social networking and other forms of social technology now offers an alternative method of connecting and engaging members within a community. In comparison to face-to-face interactions, programs that involve web-based communication can bypass location related restrictions and allow people to extend their relationships with the wider community. However, it has been found that having access to social networking may not lead to less loneliness [16, 17]. This is consistent with the loneliness paradox [18] where we may be more connected than ever digitally, but not have meaningful connections that satisfy our social needs. This is not to say that digital technology is ineffective in mitigating loneliness, but what is needed is the implementation of evidence-based strategies that can be implemented or promoted within these digital platforms. One example of an online platform that has the potential to address social isolation and loneliness is Nextdoor Inc., a social networking service for neighbourhoods. The Nextdoor online platform, based in 11 countries, including the UK, Australia, and the USA, offers community members a social network opportunity and can use the platform to promote evidence-based strategies to increase the quality of social relationships (in this case neighbourhood ties). There is, therefore, opportunity to evaluate and test any evidence-based strategies aimed at improving the meaningfulness of social ties and reducing loneliness, in addition to increasing the number of social ties (i.e., reducing social isolation).

One strategy that has already shown preliminary feasibility within an online platform [19] to improve relationship ties within a community is performing acts of kindness towards others. During the COVID-19 public health crisis, communities have shown an increase in community spirit by sharing their experiences, showing solidarity, and offering help [20, 21]. There is evidence in smaller studies that acts of kindness can indeed promote wellbeing [19, 22] and improve relationship quality [23, 24]. Acts of kindness are often integrated within strengths-based positive psychology interventions which are used to increase positive affect and improve wellbeing [25, 26]. In a sample of socially anxious adults aged 29–70 years, those who performed three acts of kindness a day for 2 days each week showed greater satisfaction in their relationships with acquaintances, co-workers, friends, and close friends (*t* (40) = 2.25, *p* < 0.05, *d* = 0.35). In comparison to the other experimental conditions commonly used in this population (i.e., identifying safety behaviours, and documenting life events), performing acts of kindness was the only condition shown to be significant in increasing participant’s satisfaction with their social relationships. Therefore, engaging in acts of kindness appears to increase relational functioning [23]. In another study, kindness and gratitude-based positive psychology activities (PPA) were used to elicit positive social interactions with peers and improve relationship satisfaction [24]. In a randomised controlled trial (RCT), 225 participants aged 18 to 66 years were assigned to one of three conditions (relationship-focused, self-focused or control). Participants reported on relationship satisfaction, social support, and happiness across three time points (baseline, post-intervention and six-week follow up). The experimental PPAs included (1) relationship-focused (involving either doing gratitude or kindness activity) or (2) self-focused (no social interaction). Those who completed relationship- focused PPAs reported greater increases in relationship satisfaction compared with those in the self-focused and active control condition at follow-up. Additionally, those in the relationship-focused condition reporting feeling their existing friendships had improved at the end of the intervention and effects remained at follow up. Taken together, PPAs that promote kindness and gratitude can improve relationship satisfaction.

In terms of reducing loneliness, there is also emerging evidence that positive psychology interventions that include doing acts of kindness hold the potential to reduce loneliness (amongst other benefits, including improving psychological wellbeing, positive affect, mental health) in people with and without mental health disorders [27–29]. But what remains unknown is the impact of acts of kindness within larger scale community interventions, particularly when assessed outside a larger toolbox of positive psychology strategies (e.g., increasing positive affect). While acts of kindness are often promoted, the effects of those are poorly understood and rarely examined within rigorous study designs. For example, do acts of kindness improve community ties (e.g., neighbours)? And if so, what is the dose response and duration require? In other words, how many acts of kindness does one have to carry out (and over what duration) before we detect an increase in relationship quality and improvements in health and wellbeing? Answers to those questions are largely unknown because there has been little focus on the evaluation of community interventions.

### Objectives

The overall objective is to examine the social and psychological impact of kindness on a community sample. This will be examined by asking community members within an online social networking platform, Nextdoor, to participate in performing at least four acts of kindness over a four-week period. We refer to this as the Kindness Is Nextdoor (KIND) challenge.

The primary intervention objective of the Nextdoor KIND Challenge is to reduce loneliness in the Nextdoor online communities across three countries (Australia, United States, United Kingdom). We expect significant changes to loneliness. Specifically, it is anticipated that challenge participants will show significantly greater improvement in loneliness compared with the control group, after accounting for known covariates.

A secondary intervention objective of the Nextdoor KIND Challenge is to reduce social isolation risk in the Nextdoor online communities across three countries (Australia, United States, United Kingdom). It is anticipated that challenge participants will show significantly greater reduction in social isolation when compared with the control group.

An additional secondary intervention objective of the KIND Challenge is to improve neighbourhood relationship quality and contact, and we expect significant improvements in neighbourhood ties both in terms of relationship quality and contact. It is anticipated that KIND Challenge participants, compared with the control group, will show greater improvement in neighbourhood relationship quality as measured by social cohesion and trust, perception that their neighbourhood is improving, higher importance around getting to know their neighbours, greater positivity and lower negativity towards their neighbors, and lower neighbourhood conflict. It is anticipated that KIND Challenge participants compared with the control group will also report significantly more neighbourhood contacts compared with the control group.

There are further secondary objectives of the KIND Challenge to improve mental health outcomes, that is lower depression, social anxiety, and stress levels, improve quality of life, and increase positive affect, with those participants in the KIND challenge showing greater positive effects when compared with control participants.

We also anticipate that acts of kindness will be feasible, acceptable, and safe to do for community participants (see apriori in Implementation secondary outcomes section).
Hypothesis 1 (H1): There will be a reduction in loneliness in participants assigned to the Nextdoor KIND Challenge groups compared to the waitlist control group post the 4-week intervention.Hypothesis 2 (H2): There will be a reduction in social isolation in participants assigned to the Nextdoor KIND Challenge groups compared to the waitlist control group post the 4-week intervention.Hypothesis 3 (H3): There will be an improvement in neighbourhood relationship quality and contact outcomes (a) social cohesion and trust, (b) perception that their neighbourhood is improving, (c) higher importance around getting to know their neighbours, (d) more likely to be classed as having a supportive neighbour network than not, (e) have lower neighbourhood conflict, and (f) increased number of neighbourhood contacts, in participants assigned to the Nextdoor KIND Challenge groups compared to the waitlist control group post the 4-week intervention.Hypothesis 4 (H4): There will be an improvement in mental health secondary outcomes, lower (a) depression and (b) social anxiety, (c) stress, and greater (d) quality of life, and (e) positive affect, in participants assigned to the Nextdoor KIND Challenge groups compared to the waitlist control group post the 4-week intervention.

While it is vital to investigate the impact of KIND Challenge post intervention, it is possible for impact on outcomes to be distal; that is indirect effects caused by changes in proximal outcomes. The KIND Challenge aims to reduce loneliness and social isolation, which may lead to later distal impact on other outcomes. Capturing impact at one-month follow-up after the completion of the KIND Challenge enables modelling the maintenance of intervention effects, i.e., are effects sustained at one-month or are sleeper effects present? In addition to understanding whether effects of the intervention are sustained, it is also important to know whether the intervention itself is sustainable. The KIND Challenge acts are positive, engaging, and feasible to the average individuals, and thus designed to be sustainable.
Hypothesis 5 (H5): The Nextdoor KIND Challenge effects noted in H1–4 above will be maintained at one-month follow-up for the participants randomly allocated to KIND Challenge group.Hypothesis 6 (H6): The KIND Challenge is sustainable, participants assigned to the KIND Challenge will continue engaging in acts of kindness at one-month follow-up.

The third objective of this intervention is to examine factors that may moderate the effects, including dosage, pre-existing levels of social connection, type of kindness activity, and adherence. Interventions are rarely adhered to in full, and variability in compliance and engagement is commonplace; moreover, this variability is associated with differences in expected outcomes. It is therefore important to take measures of engagement with the intervention to explore how variability in engagement moderate outcomes. First, it is anticipated that the level of adherence (do participants complete the instructed four acts of kindness) and engagement, or *dosage*, in terms of frequency and duration of KIND activity will make a difference to loneliness and social isolation severity. Second, the more connected participants feel in relation to the KIND activity will impact outcomes and participants are likely to feel less lonely. Third, it is recognized that some acts of kindness may have greater effect than others, and specifically how do different acts of kindness that provide either emotional, tangible, informational, belonging, or companionship support impact on loneliness and social isolation will be examined. Therefore, both quantity and quality of engagement with the KIND challenge can be modelled as predictors of primary outcomes of loneliness and social isolation. Finally, understanding engagement and adherence to the intervention is fundamental to exploring the feasibility and making recommendations for future interventions. Therefore, an additional purpose of the study is to identify reasons, (i.e., lack of time, illness, work, stress etc.) for lack of engagement and adherence to the KIND challenge. In terms of analysis, traditional approaches to dealing with (non) compliance in RCTs (e.g., ‘as treated’) produce biased estimates, so we will use Complier Average Causal Effect (CACE) estimation to explore the impact of compliance to implementing the intervention. CACE allows exploration of treatment effects where there is less than ideal levels of participant compliance (as opposed to the offer of said intervention, as in ITT used for H1 above).
Hypothesis 7 (H7): The impact of the Nextdoor KIND Challenge on the primary outcome of loneliness and secondary outcomes of social isolation, neighbourhood relationship quality and contact, neighbourhood connectedness, and mental health will vary as a function of intervention adherence and engagement. Specifically, we would predict larger effect sizes for participants who (a) adhered and engaged more in the KIND Challenge and (b) feel more connected to their neighbours, and (c) we would predict that levels of engagement with different acts of kindness, i.e., emotional support, tangible support, informational support, belonging support, and companionship support to have different effects.Hypothesis 8 (H8): The magnitude of intervention effects noted in H1–4 above will vary as a function of intervention compliance. Specifically, we predict larger effect sizes for participants classified as compliers in terms of number of kind acts completed (dosage).

The final objective of this intervention is to explore additional factors that may influence participants’ experiences or the effectiveness of the intervention. These relate to (1) how loneliness and social isolation differ across countries, (2) how loneliness and social isolation differ across neighbourhood characteristics (urban vs rural), and demographic variables (age, gender, socioeconomics), (3) how COVID-19 impacts loneliness and social isolation, and on people’s interactions with their neighbours. Consistent with the evaluation of community-based interventions, the role of demographic and particular neighbourhood characteristics should be incorporated as potential covariates in the analyses.

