### Waitlist condition

It will be clearly outlined to participants that the trial involves a waitlist control prior to enrolment, and informed consent will include agreement to undergo a 4-week waitlist period and an additional assessment prior to commencing the KIND Challenge. Waitlist participants will be instructed to continue with their usual activities throughout the waitlist period. Waitlist participants received one email 2 weeks prior to remind them of their upcoming enrolment into the Challenge condition.

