#### Pre-KIND challenge neighbourhood contact and previous kindness activity

Prior neighbourhood contact may influence both the primary outcome and participation in the Challenge. Thus, participants will be asked if they have been in contact with their neighbour safely in person or using a digital communication device (Yes/No). They are then asked if they had completed an act of kindness before being assigned to the Challenge. If yes, participants will be asked how frequently they completed the activity (1 = once to 4 = more than 5 times), the duration of the activity (1 = less than 10 min to 5 = more than 2 h) and how connected they feel to their neighbours because of the activity (1 = not at all connected to 10 = very connected). These questions were specifically developed for the study (see Supplementary Table 1 – section j).

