### Adherence and engagement variability

Variability in adherence and engagement will be measured in the participants allocated to the KIND Challenge group. First, adherence can be measured by the frequency and duration of KIND acts completed during the 4-week intervention. Second, an index of level of engagement for each type of activity completed (i) emotional support, (ii) tangible support, (iii) informational support, and (iv) belonging support, (v) companionship support can be created by combining the frequency and duration to produce an indicator of dosage for each type of KIND act. Third, the impact of overall engagement with the KIND Challenge can be modelled via meaningfulness, degree of positive feelings and sense of connectedness to others.

Linear multiple regression modelling in Mplus 8.3, will be employed to model the adherence and engagement as predictors of post 4-week intervention outcomes (H7), across the primary outcome of loneliness, and secondary outcome of social isolation, a neighbourhood relationship quality and contact, neighbourhood connectedness, and mental health. As with the H1–4 the model building approach will be used.

Reasons for non-compliance will also be captured and explored to assess barriers and challenges to competing the KIND activity, as measured by frequencies of lack of time, forgot, illness, work stress, family pressures or other.

CACE estimation will be employed using Mplus 8.3 to examine whether the effects noted in ITT analyses (H1–4) change once intervention compliance is taken into account. Participant demographics and baseline outcome variables will be used as predictors of the latent class compliance variable. Compliance will be assessed via dosage (i.e., number of kind acts completed; compliers vs. non-compliers). The CACE analysis will follow the same regression model building approaches detailed in H1–4.

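### H8 is nearly true by construction: a complier effect larger than the ITT effect is no evidence that more acts help, and the planned CACE may be biased in either direction

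*Protocol article*

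**What the plan says.** Under Objectives in the Protocol article, H8 predicts that intervention effects vary with compliance: "we predict larger effect sizes for participants classified as compliers in terms of number of kind acts completed (dosage".

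The section Adherence and engagement variability gives the method. CACE estimation in Mplus is used "to examine whether the effects noted in ITT analyses (H1–4) change once intervention compliance is taken into account". The split is binary and based on a count: "Compliance will be assessed via dosage (i.e., number of kind acts completed; compliers vs. non-compliers". Class membership is modelled: "Participant demographics and baseline outcome variables will be used as predictors of the latent class compliance variable". That text names no cut-off. The number four appears in Objectives as a gloss on adherence ("do participants complete the instructed four acts of kindness") and in the description of what participants are asked to do.

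On exposure by arm, the same section says: "Variability in adherence and engagement will be measured in the participants allocated to the KIND Challenge group". Under Waitlist condition: "Waitlist participants will be instructed to continue with their usual activities throughout the waitlist period". Table 1 nevertheless schedules the previous-kindness item at T2, which only the waitlist completes. Its text reads: "They are then asked if they had completed an act of kindness before being assigned to the Challenge", with frequency and duration to follow. The CACE plan does not use these answers as exposure.

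**The concern.** A hypothesis should be able to come out false. If the estimator makes the complier effect larger than the ITT effect whatever the acts do, then finding it larger says nothing about dose. The Background names dose response as an open question and H8 carries the label dosage, so readers would naturally take a confirmed H8 as an answer to it.

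The size of the CACE matters too, because it would be reported as the effect among those who did the acts. It rests on who counts as a complier and on the waitlist having no exposure. The acts include ordinary neighbourly behaviour such as a chat across the fence, and Allocation and blinding concedes that enrollees may already be more altruistic.

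**Working it through.** **1. The protocol's own figure.** Sample size gives 1500 per country, up to 20 covariates, power 0.80, alpha 0.05 and a lowest pre-post correlation of .35; allocation is 1:1. Two-sided testing is assumed.

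MDES = (t for alpha/2 + t for power) × √[(1 − R²)/(P(1 − P)n)], with R² = 0.35² = 0.1225 and df = 1500 − 20 − 2 = 1478.

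= 2.80 × √(0.8775/375) = 0.136, which rounds to the stated .14. I use 0.14 as the ITT effect below.

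**2. CACE against ITT.** With no effect in non-compliers and no exposure among controls, CACE = ITT/π, where π is the complier share. The protocol gives no π, so these values are assumed:

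| π | CACE |
|---|---|
| 0.30 | 0.14/0.30 = 0.467 |
| 0.50 | 0.14/0.50 = 0.280 |
| 0.70 | 0.14/0.70 = 0.200 |
| 0.90 | 0.14/0.90 = 0.156 |

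The ratio CACE/ITT is 1/π, which depends on compliance alone. Comparing compliers with non-compliers instead does not help, since the latter are set to zero.

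**3. The latent-class form.** The protocol plans a covariate-predicted latent class, for which the ratio is only approximate. I simulated 300 trials per scenario: n = 1500, about 50% compliers, one baseline covariate with coefficient 0.35, compliers 0.2 SD less lonely regardless of arm, and the exclusion restriction imposed. The table gives the share of trials in which CACE exceeds ITT in size.

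| True complier effect (SD; negative = less lonely) | Ratio form | Latent class | Latent class, same sign as ITT |
|---|---|---|---|
| −0.28 | 100% | 99% | 99% |
| −0.10 | 100% | 95% | 92% |
| 0 | 100% | 89% | 83% |
| +0.28 | 100% | 100% | 99.7% |

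The simulation error on the 89% is √(0.893 × 0.107/300) = 0.018.

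**4. Partial doers, if the cut-off is four acts.** Assume 50% of the KIND arm do four or more acts, 30% do one to three, and a partial doer gains a fraction ρ of the full effect. The planned value is 0.14/0.50 = 0.28. The full-dose effect is 0.14/(0.50 + 0.30ρ).

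- ρ = 0.25: 0.14/0.575 = 0.243; planned/true = 1.15
- ρ = 0.50: 0.14/0.65 = 0.215; planned/true = 1.30
- ρ = 1: 0.14/0.80 = 0.175; planned/true = 1.60

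**5. Waitlist kindness.** Assume 60% of the KIND arm reach the cut-off. The planned value is 0.14/0.60 = 0.233. If a share q of the waitlist also reaches it, the correct value is 0.14/(0.60 − q).

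- q = 0.10: 0.280; planned/true = 0.83
- q = 0.20: 0.350; planned/true = 0.67
- q = 0.30: 0.467; planned/true = 0.50

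**6. Both together** (50% full, 30% partial, ρ = 0.5). The true effect is 0.14/[0.65 − (full share in waitlist + 0.5 × partial share in waitlist)].

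- No waitlist kindness: 0.14/0.65 = 0.215; planned/true = 1.30
- 10% full, 10% partial: 0.14/0.50 = 0.280; planned/true = 1.00
- 30% full, 20% partial: 0.14/0.25 = 0.560; planned/true = 0.50

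**The case against.** A reader might infer that H8 cannot fail at all. That is exact only for the ratio form. The latent-class model gave a CACE smaller in size than ITT in about 11% of the null trials. If H8 is read as predicting a larger benefit, it also fails when the ITT effect goes the wrong way. H8 names no comparator, and Objectives presents CACE as exploration. These points change the wording from certain to nearly certain. They do not make the comparison informative, because a result expected in about nine of ten trials with no effect is not a test.

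A reader might also infer that the planned CACE is inflated. The protocol does not support that. Inflation from partial doers needs a four-act cut-off, which the CACE text does not set; with a cut-off of one act those participants are compliers. A numerical threshold may properly sit in an analysis plan that is not shown, so its absence is not the finding. Ignoring waitlist kindness works the other way.

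H7 does model frequency and duration as predictors of outcome, so dose is not wholly neglected, but adherence there is measured within the KIND arm and is not randomised.

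Finally, the exposure items are not well matched. KIND participants rate each activity in frequency bands over the past month, while the previous-kindness item states no look-back period. That limits any two-arm exposure model, though not a table of acts by arm.

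**Conclusion.** The point holds for H8 as a hypothesis. Judged by CACE against ITT, it is confirmed in size almost by construction: 100% of simulated trials in ratio form and 89% to 100% in latent-class form, including with no effect. It cannot support a claim that more acts give more benefit. This rests on the non-complier effect being fixed at zero, which is the standard identifying assumption but is not stated in the article.

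The bias in the CACE itself is possible but of unknown sign. In the illustrations, planned/true ran from 1.60 with partial doers alone to 0.50 with waitlist exposure. All compliance and exposure shares are assumptions, because the protocol gives none. H8 is a supplementary analysis, and the ITT analyses of H1–4 do not depend on it.

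**What to change.** 1. Restate H8 as estimation of the complier effect with its confidence interval. Drop the prediction of larger effects in compliers as something to be confirmed, and say that a CACE above ITT will not be read as support for a dose effect.
2. State the exclusion restriction, and show as a sensitivity analysis how the CACE changes between cut-offs of at least one act and four acts.
3. Tabulate kindness acts by arm (KIND at T3, waitlist at T2). As far as the items can be matched, add a sensitivity CACE that allows for exposure in the control arm.

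The cost is wording and some extra model runs on items already scheduled. The price is a less favourable H8 claim and, once control exposure is allowed for, a wider interval. The CACE itself may go up or down.
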